### 2.7 Secondary study outcomes

Secondary study outcomes will be assessed at multiple timepoints (Table 2) pre- and post-intervention.

#### 2.7.1 Body structure and function

*Passive range of motion* (ROM) of selected movements (hip flexion contracture; hip abduction; popliteal angle; knee flexion contracture; ankle dorsiflexion with knee flexed or extended), and evaluation of resting and dynamic spasticity as measured by the *Tardieu Scale* (Scholtes et al., 2006) at knee and ankle (hip adductors, hamstrings, gastrocnemius with knee flexed and extended) will be conducted at all functional assessment timepoints. This is important to establish at baseline (excerpted from screening session data where ROM eligibility was confirmed) to monitor adverse events, and permit evaluation of changes in ROM associated with Trexo use.

#### 2.7.2 Postural control assessments

Two postural assessments will be administered by the physiotherapist assessor, and scored from video that will be captured during the assessment by a research assistant using a standardized camera angle protocol.

The *Posture and Postural Ability Scale* (PPAS; Rodby-Bousquet et al., 2016) is a validated measure for children with CP in GMFCS levels II to V. It will rate the symmetry and alignment of the child’s head, trunk, pelvis, legs, arms, and weight distribution in frontal and sagittal planes. The child will be guided into prone, supine, sitting and supported standing positions (30 s in each) by the assessor. Scoring will be done from the video of the assessment.

The *Level of Sitting Scale* (LSS) (Fife et al., 1991; Field and Roxborough, 2011) is designed for children who are wheelchair users and require some degree of external support (GMFCS IV and V). The LSS will classify a child’s sitting ability without feet supported. It will serve as both a descriptive measure of children enrolled in the study and also an outcome measure in tandem with the PPAS. It will be scored from the PPAS video.

#### 2.7.3 Functional abilities parent-report questionnaire

The *Pediatric Evaluation of Disability Inventory* (PEDI-CAT) (Haley et al., 2011; Shore et al., 2017) parent-report questionnaire’s Daily Activities (speedy version), Mobility (content version) and Social/Cognitive (speedy version) domains will be completed by the child’s parent at each of the functional assessments, via a secure weblink on a study tablet. If both the parents are present, they may complete it together.

#### 2.7.4 Gait assessments

Functional gait will be assessed via a *1-minute walk test* (1MWT) (Hassani et al., 2014) and the *Directional Mobility Assessment* (DMA) (Wright and Jutai, 2006; Livingstone and Paleg, 2016), done in the child’s regular walking device (if they use one) and the Trexo walker. The 1MWT will measure the distance walked down a straight wide hallway within 60 s with the Trexo and with the child’s regular walker, with support from the child’s PT/PTA team as needed for steering (Trexo and regular walker) and facilitating steps (regular walker). The DMA incorporates a functional walking course: straight walking, turns, obstacles, narrow path, and backing up.

These walking tasks will be administered by the child’s treating PT/PTA simultaneously during MMG/heart rate monitoring (facilitated by study researchers). Involvement of the PT/PTA in this testing is essential as they are Trexo-trained and aware of the child’s functional abilities and safety considerations. A video recording will be made of these walking tests to permit their rating by an independent PT assessor to maintain independence of scoring from the clinical team.

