i)Assess aspects of clinical feasibility, safety, and acceptability of Trexo gait training within an outpatient center and schoolii)Capture the Trexo user experience of children and physiotherapists during exoskeleton gait training, as well as physiotherapists’ and parents’ perspectives of outcomes associated with useiii)Assess motor and functional outcomes pre/post Trexo gait training (including any carryover effects)iv)Examine brain anatomy and brain connectivity pre/post Trexo gait trainingv)Evaluate muscle activations, particularly indicating muscle fatigue, during Trexo gait training (compare with muscle activations during use of regular assistive mobility devices)vi)Capture heart rate and heart rate variability during Trexo gait training (compare with heart rate during use of regular assistive mobility devices).

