## 2 Methods and analysis

### 2.1 Study design

This mixed methods feasibility study protocol [phase IIa; Orbit Model (Czajkowski et al., 2015) uses an **O_0_ X O_1_ O_2_** design (Figure 1), with participants (*n* = 10) acting as their own controls (within a longitudinal intervention consisting of O_0_, O_1_, and O_2_ = study assessment phases, and X = physiotherapy intervention with the Trexo]. The protocol follows Standard Protocol Items: Recommendations for Interventional Trials (SPIRIT Checklist; Chan et al., 2013a,b). All study team members’ roles are outlined in Table 1.

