**FIGURE 1 F1:**
[figure not shown]
Flow chart of study visits and timeline, reflecting O_0_ X O_1_ O_2_ design.

**TABLE 1 T1:** Research team member designations and corresponding roles in the study.

Designation	Role
Principal investigators	Responsible for study oversight and adverse event management.
Study researchers	Non-PT team members that are responsible for coordinating recruitment, scheduling, non-PT data collection, and data analysis.
Study physician	Center-affiliated pediatrician that helps with diagnostic expertise, recruitment, eligibility, and adverse event management.
Treating PTs/PTAs	Physiotherapy team members that are Trexo-trained and complete the 12 Trexo (twice weekly) intervention sessions.
PT assessors	Independent PTs (different from treating PTs) that complete the physical screening and motor/functional assessments.
Study interviewer	Independent team member that hosts all Zoom-based interviews.
MRI technician	Centre-affiliated technician that operates MRI scanner.

During ‘**O’ phases (pre/post intervention)**, participants will do their usual physiotherapy regimen (with their usual assistive device, where applicable) and associated home program, and will undergo the set of study assessments (gross motor/functional assessments and neuroimaging) in this approximately 2–3-week period pre- and post-Trexo use (Phase X). One-month post O_1_, participants will have one final motor/functional assessment and neuroimaging visit (O_2_). They will continue with their usual physiotherapy regimen during the month between O_1_ and O_2_.

**Intervention ‘X’ phase** will consist of the Trexo physiotherapy block: physiotherapy sessions twice weekly (30-min sessions excluding initial set-up time) for 6 weeks provided by a study-trained PT/Physiotherapist Assistant (PTA) team within a goal-based training program that is grounded in motor learning principles. Trexo physiotherapy will be integrated within a school-based program for half of the study cohort (*n* = 5), and within an outpatient program for the other half (*n* = 5). Each child will receive 1–2 acclimatization/fitting sessions in the Trexo before starting physiotherapy sessions. Walking tests and muscle recordings at the start and end of this phase will be done in the Trexo and in the child’s usual non-robotic wheeled walker (if they use one) for comparison and for assessment of potential carryover effects from Trexo use to their wheeled walker.

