#### 2.4.3 Outpatient physiotherapy program

Participants in the outpatient cohort will receive two individual Trexo-based physiotherapy sessions per week (30-min sessions active treatment time excluding initial Trexo set-up time). The session will be led by one of the study’s Trexo-trained PTs along with a Trexo-trained assisting PTA. These clinicians will not necessarily be previously familiar with the child, being assigned instead according to family and PT/PTA availability. To ensure safe and effective communication with the child, parents will be present at all sessions and will help interpret communication and fatigue as needed while the child is in the Trexo. For each session, 60 min will be allocated to setup, Trexo-based physiotherapy, and session feedback documentation by the PT/PTA. Sessions will occur in the center’s gait lab, hallways, or outdoors in the summer months.

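### In the regular walker, a change in 1MWT distance mixes the child's own stepping with manual help that may vary, and independent video scoring of distance does not separate the two

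*Protocol article*

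**What the plan says.** Objective iii in the Introduction is to "Assess motor and functional outcomes pre/post Trexo gait training (including any carryover effects"). Section 2.1 (Intervention X phase) puts walking tests and muscle recordings at the start and end of the block, in the Trexo and in the child's usual wheeled walker if there is one, "for comparison and for assessment of potential carryover effects from Trexo use to their wheeled walker". Children are described as "acting as their own controls"; there is no comparison group.

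Section 2.7.4 defines the outcome: "The 1MWT will measure the distance walked down a straight wide hallway within 60 s". In the same sentence it allows support from the child's PT/PTA team "as needed for steering (Trexo and regular walker) and facilitating steps (regular walker"). Step facilitation is thus named for the regular walker only. On who runs the tests: "These walking tasks will be administered by the child’s treating PT/PTA simultaneously during MMG/heart rate monitoring". The stated safeguard is a video of the tests, made "to permit their rating by an independent PT assessor to maintain independence of scoring from the clinical team".

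Table 2 lists the 1-minute walk and the Directional Mobility Assessment (DMA) as secondary outcomes, done in both devices at the beginning and end of the intervention phase. Section 2.11.1 plans paired t-tests or non-parametric equivalents between baseline and post-intervention for the co-primary measures and then for each secondary outcome.

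**The concern.** Distance in 60 s is a sound before-and-after measure only if whatever produces it, other than the child, stays the same. Here a second contributor is allowed, the amount of help is left to judgement on the day, and the helpers are the team that delivered the intervention. If they facilitate more steps at the second test, distance can rise with no change in the child. If the child has become more independent and is helped less, distance can stay the same or fall although carry-over has occurred.

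At stake is the reading of one piece of the carry-over evidence. It is the piece that most directly shows walking in the non-robotic device, so readers are likely to give it weight. With no control group, nothing else in the design separates a change in handling from a change in the child.

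**Working it through.** The document gives no standard deviation, expected change or power for the 1MWT, and section 2.2.4 justifies the 10 children descriptively. There is no figure to reproduce, so the check is mainly one of reasoning.

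**Step 1. What each provision covers.**

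| Provision | Section | Covers scoring of distance | Covers help given during the test |
|---|---|---|---|
| Independent PT rates the video | 2.7.4 | Yes | No, as stated |
| Treating PT/PTA administers the test | 2.7.4 | No | They supply the help |
| Detailed session documentation by a researcher | 2.5.3 | No | Described for the physiotherapy sessions, not the walking tests |
| Same independent assessor per child, blinded to previous results | 2.1 | Applies to the motor/functional assessments | No |

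**Step 2. Why distance alone cannot separate the two.** Let c be child-initiated steps in 60 s, h facilitated steps and s step length, taken as constant. Then D = s(c + h), and the start-to-end change is ΔD = s(Δc + Δh). Carry-over concerns Δc. Measuring D perfectly at both tests gives one equation with two unknowns. Better scoring of D does not help; information on h does.

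**Step 3. Direction and possible size (all values assumed).** Let f = h/(c + h) be the facilitated share.

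- If facilitated steps simply add to a fixed c, D is proportional to 1/(1 − f). Raising f from 25% to 50% gives (1/0.50)/(1/0.75) = 1.50, a 50% longer distance with no change in the child. Lowering f from 50% to 25% gives 0.67, a 33% shorter distance.
- If facilitated steps displace the child's own within the 60 s, so that c + h is fixed, the same shifts in f change D by 0%. Then a fall in f from 50% to 25% means c rises from 0.50 to 0.75 of the total, a 50% gain in own stepping that distance does not show.

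For this one assumed pair of shares, the effect on distance runs from −33% through 0% to +50%. The document does not say which model applies or what f is.

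**Step 4. Effect on the planned paired test (all values assumed).** Suppose there is no true carry-over and a change in help shifts mean distance by d standard deviations of the paired differences, always in one direction. The chance of a significant two-sided result at an assumed α of 0.05 is P(|T| > t(0.975, n − 1)), with T noncentral t and noncentrality d√n. For n = 10 and d = 0.5 the noncentrality is 0.5 × √10 = 1.58. Values of n below 10 are shown because owning a walker is not required (section 2.2.2).

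| d | n = 5 | n = 8 | n = 10 |
|---|---|---|---|
| 0 | 5% | 5% | 5% |
| 0.3 | 8% | 11% | 14% |
| 0.5 | 14% | 23% | 29% |
| 1.0 | 40% | 68% | 80% |

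This shows what a consistent shift would do. It is not an estimate for this study: if help rises for some children and falls for others, the effect is added noise and a smaller mean shift.

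**The case against.** Several points on the other side are right and limit the finding.

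- A reader might infer that carry-over is judged from the 1MWT alone. It is not. Section 2.1 also names muscle recordings, the walking tests include the DMA, and treating PTs may set Goal Attainment Scaling goals tied to the regular walker (section 2.6.2). Objective iii covers motor and functional outcomes generally, including the GMFM-88 by an independent assessor, the parent-rated COPM and the PEDI-CAT. None of the last three depends on this test.
- A reader might infer that the therapist moves the child's legs. The text speaks only of facilitating steps by the PT/PTA team, which may be much less. The additive model in the working leans on the stronger reading and is therefore only an illustration.
- A reader might infer that the bias favours the Trexo because the team comes to know the child. Section 2.4.3 says of outpatient staff that "These clinicians will not necessarily be previously familiar with the child", but in the school half the child's usual school PT delivers the sessions (section 2.4.4), so the PT is familiar from the start. The document states nothing about what the team expects to see.
- An article condenses the full protocol, and test manuals or forms may grade assistance. That cannot be checked here, and it may well apply to DMA scoring.
- Help is inherent in this population. Eligible children walk short distances only, with a maximum support walker and caregiver assistance (section 2.2.2), and section 2.7.4 justifies the treating team's role by training and safety.

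What stands is what the article itself fixes: an outcome of distance, a rule that help is given as required, and a safeguard aimed at scoring. Those three together leave the 1MWT change ambiguous. That children need help is the reason to record it, not a reason to ignore it.

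**Conclusion.** The point holds in a limited form. In the regular walker, the start-to-end change in 1MWT distance can reflect a change in manual help, in either direction, as well as carry-over, and independent scoring of distance from video does not tell them apart.

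The size of the bias cannot be derived from the document. The percentages for distance and for false-positive results rest on assumed shares, shifts and α, and should not be quoted as properties of this study. Nor does the document support the reading that the whole carry-over conclusion fails or that the error must run towards benefit. The measure affected is one secondary outcome in a feasibility study of 10 children, fewer if some have no walker. The co-primary GMFM-88 and COPM are untouched.

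It still deserves a change: carry-over is part of a stated objective, the paired analysis will be run, and the video needed to resolve the ambiguity is already planned.

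**What to change.** 1. On the regular-walker 1MWT form, add a field for the level of manual step help, completed at both the start-of-block and end-of-block tests.
2. Have the already planned independent assessor grade assistance from the existing video, or count child-initiated and facilitated steps.
3. Report each child's 1MWT distance together with the help level at both tests.
4. State the reading rule in advance. A longer distance is interpreted as carry-over only when help did not increase. Less help at similar distance is possible carry-over. A longer distance with more help, or a shorter one with less, is reported as not interpretable for carry-over. As the study is uncontrolled, even the favourable patterns remain descriptive.
5. Do not script the start-of-block level of help at the end test. That would impose help that an improved child may no longer need and could hide the gain in independence the test is meant to detect.

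The cost is one form field, one scoring item and a few more minutes of rating per video. No new visit, device or recording is needed, and who helps the child and when stays as the protocol has it.

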#### 2.7.5 Heart rate

*Heart rate* during gait will be captured using a Polar H10 Heart Rate Sensor (wireless chest strap placed around the torso) which will transmit data (beats per minute, RR intervals, and heart rate variability taken continuously) via Bluetooth to a secure device. Heart rate will be captured post-intervention (end of Phase X) concurrently with muscle recordings (section “2.6.4 Muscle recordings”) during Trexo and regular walker use at the timed walk and DMA assessments since robotically facilitated walking may impact heart rate differently than would a manual walker. Resting heart rate will be captured initially in each instance. Heart rate will also be captured in the absence of walking, during the post-intervention functional assessment.

### 2.8 Participant characterization

The following assessments will be completed only once during the child’s study participation as they portray a fixed trait/ability (i.e., not outcome measures). These assessments will help characterize each participant and may serve as predictors or correlates for feasibility and outcome measure results.

#### 2.8.1 Upper extremity function

The *Manual Ability Classification System* (MACS or MiniMACS; Eliasson et al., 2006) will be completed by a PT assessor at the end of the baseline motor/functional assessment as they reflect the child’s hand function observed during upper and lower body tasks in the assessment and confirm child’s day to day hand function in conversation with the parent- at the assessment. Children in GMFCS IV may have hand function at a different level than that of their gross motor function, and these hand and arm abilities may have an impact on what the child will be able to do during Trexo physiotherapy. Hence this information may be important in the interpretation of sessional data and ultimate goal accomplishment.

#### 2.8.2 Communication ability

The *Communication Function Classification System* (CFCS; Hidecker et al., 2011) will be used after all 12 Trexo physiotherapy sessions have been completed, to capture the child’s communication style over time while in the Trexo.

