**Participant characterization**					
MACS*	PT assessor with parent	•			
CFCS	Treating PT and SR			**T**	
Dimensions of mastery*	Parent	•			
Trexo physical adjustments	Treating PT and SR		**T**		

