**PT and parent perspectives**					
Parent baseline interview	Parent with SI		•		
Parent outcomes interview	Parent with SI			•	
PT training interview	Treating PT/PTA with SI			•	
PT outcomes interview	Treating PT/PTA with SI			•	

*Completed during motor/functional assessment visit. **T** = done in Trexo; **W** = done in regular walker; • = done without any device. (†) denotes the beginning of the intervention phase and (‡) denotes the end of the intervention phase.

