### 2.9 PT and parent perspectives

Qualitative interviews will be scheduled separately with the PT/PTA team and parents with an independent study interviewer using semi-structured interview guides. These interviews will be scheduled proximal to the pre- and post-intervention study timepoints.

Participating PTs and PTAs will have the opportunity to share their perspectives via two optional interviews: (i) reflection on the strengths and limitations of the Trexo training process used following the completion of their training and a round of Trexo physiotherapy sessions for at least one child (∼30–60 min); and (ii) Trexo user experience for each participant, following the end of that child’s physiotherapy intervention (60–90 min).

Parents’ study expectations and goals will be collected at two optional interview timepoints: (i) baseline; about Trexo outcomes goals and hopes (∼20 min); and (ii) post-Trexo intervention; focusing on observed outcomes, impressions about study methodologies, and individualized goal accomplishment including questions about overall quality of life in addition to the questions about mobility (∼45 min). Since the research team will see the child for only 2 h a week, parent feedback will be essential to capture functional changes observed in the daily living context of their child. This will also be an opportunity to solicit parental feedback on study design, tolerance, and opinions on different study aspects.

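### CFCS is labelled a fixed trait and possible predictor, but it is rated once, after the Trexo block, from communication in the device, so it cannot be read as a pre-treatment predictor

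*Protocol article*

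**What the plan says.** The introduction to section 2.8 says its assessments are done only once because "they portray a fixed trait/ability (i.e., not outcome measures"), and that they "may serve as predictors or correlates for feasibility and outcome measure results".

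Section 2.8.2 places the CFCS "after all 12 Trexo physiotherapy sessions have been completed" and gives its purpose: "to capture the child’s communication style over time while in the Trexo". In Table 2 the CFCS row has a single entry, under O1, with the mark for a measure done in the Trexo. The people responsible are listed as "Treating PT and SR".

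The other two trait measures in section 2.8 are taken before treatment. MACS is rated by a PT assessor at the end of the baseline motor/functional visit and checked with the parent against day-to-day hand function (2.8.1). Dimensions of Mastery is completed by the parent at baseline only (2.8.3).

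**The concern.** A variable used to predict response should be fixed before the treatment can affect it. CFCS as planned summarises behaviour during the treatment. A child who is comfortable and engaged in the device may communicate more there and be rated accordingly. A child who finds it tiring or distressing may do the opposite. The rating may then contain some of the response it is meant to predict.

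The rating is also made in part by the clinician who delivered the sessions, at a time when that clinician knows how the block went and scores GAS, which Table 2 lists as a primary outcome.

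If CFCS were then correlated with goal attainment or session indicators, an association could not be read as showing that children who communicate better beforehand do better. It could equally mean that children for whom the sessions went well communicated better in them, or that one rater's impression shaped both scores.

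**Working it through.** No arithmetic applies. The check sets the relevant places in the protocol article side by side.

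1. **Timing.** MACS: O0. Dimensions of Mastery: O0. CFCS: O1 only. Screening records how the child signals discomfort or pain (2.3.2), but that is not a CFCS level. No pre-treatment CFCS value exists to fall back on.

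2. **Basis of the rating.** MACS draws on observation at the baseline visit and on daily life. CFCS draws on communication across the sessions in the device. Section 2.1 has children on their usual regimen in the O phases, so a rating at O1 marked as done in the Trexo has to look back over phase X. It is retrospective and made with the course of treatment known.

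3. **Setting.** In outpatient sessions parents are present and help interpret communication, and the clinicians may be new to the child (2.4.3). In school sessions parents are typically absent and the child's usual PT treats (2.4.4). The split is 5 and 5 (2.1). A rating based on these sessions may therefore vary with setting as well as with the child.

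4. **Rater overlap with outcomes.**
   - GAS: scored by the treating PT after the last session (2.6.2). It shares one of the two CFCS raters, at about the same time.
   - GMFM-88: scored by an independent PT assessor (2.6.1). No shared rater.
   - COPM: rated by the parent with the PT assessor (2.6.2). No shared rater.
   - 1-minute walk and DMA: administered by the treating team but rated from video by an independent assessor (2.7.4). No shared rater.
   - Session comfort and enjoyment: rated by the child on a picture scale (2.5.4). No shared rater.

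   So the shared-rater problem is confined to GAS and is partial there. For the other measures what remains is post-exposure measurement alone.

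5. **Planned use.** Section 2.8 allows use as predictor or correlate. Section 2.11.1 names correlations among primary and secondary outcomes and with MRI results. CFCS is in neither outcome class in Table 2, and no CFCS analysis is named.

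The label in section 2.8 and the procedure in 2.8.2 cannot both stand: a trait fixed before treatment is not measured by summarising conduct under treatment.

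**The case against.** The strongest reply is that this is loose wording in an umbrella sentence. Section 2.8 also covers the Trexo adjustment template, which is updated during the block (2.8.4) and is plainly no fixed trait. Section 2.8.2 states a deliberate purpose, communication while in the device, which a baseline rating cannot serve. The predictor role is only a possibility, correlates are named beside predictors, and no analysis of CFCS is specified. On this view it is enough to remove the fixed-trait label for CFCS.

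Much of this stands, and it limits the size of the point. It does not remove the mismatch. Removing the label would leave the study with no pre-treatment measure of communication ability, and a baseline rating cannot be recovered once a child has started. The in-device purpose is also served elsewhere, since a non-PT researcher records communication modes at every session (2.5.3).

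A reader might infer three stronger things that the document does not support:

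- **That children who stop early have no CFCS.** Section 2.10 brings the post-Trexo assessment forward for a child stopped because of continuing risk, and invites those who withdraw to the next follow-up. Section 2.8.2 gives a usual time for the rating and does not say that a rating after fewer sessions is invalid.
- **That the CFCS association will decide who suits the device.** No section says so.
- **That the parents' baseline interview is contaminated by sessions already seen.** Table 2 shows the "Parent baseline interview" in the X column, but section 2.9 describes it as "baseline; about Trexo outcomes goals and hopes", and section 2.3.3 places the parent interviews before and after the child's Trexo use. The text settles the timing. The cell is at most a labelling slip, and the table was read from PDF by a program.

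**Conclusion.** The point holds in a limited form. CFCS is described as a fixed trait with a possible predictor role, yet it is measured once, after exposure, from behaviour during the intervention, by the treating PT together with a study researcher. It cannot be read as a pre-treatment predictor of anything measured during or after the block. The problem is greatest for GAS, where one rater is shared, and weaker for GMFM-88 and COPM.

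The rating procedure applies to all 10 children, but the consequence is modest: the sample size is justified descriptively (2.2.4) and no confirmatory result depends on CFCS. The conclusion assumes that CFCS may be used as section 2.8 allows. If it is only reported as a description of communication in the device, what remains is a wrong label. That in-device communication reflects response to treatment is plausible but not shown in the document. The argument needs only that this cannot be ruled out.

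**What to change.** Have the PT assessor rate CFCS with the parent at the O0 motor/functional visit, next to MACS, from everyday communication. Use only that level as predictor or correlate.

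If communication in the Trexo is of interest, keep the end-of-block rating under a different name as a descriptive process variable, and state that it will not be used as a predictor. If an O0 rating is not wanted, the minimum is to exempt CFCS from the fixed-trait and predictor wording of section 2.8.

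This changes the CFCS row of Table 2 and the sentence in 2.8.2. It takes a few minutes at an existing visit where assessor and parent are already present, so the downside is a slightly longer O0 visit. It has to be done before a child starts the block. As housekeeping, the Table 2 cell for the parents' first interview can be aligned with the pre-treatment timing in the text.
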